### 3.2. Aim of the study

Primarily the efficacy of the splints shall be proven. The primary endpoint is weight reduction after using the splints. Secondary endpoints regarding mode of action, safety and benefit shall be analysed, if the existing documentation and is sufficient.

Hereafter, the splints shall be standardised regarding the construction and further specified. This will form the basis for the development and certification of the medical device (MD) risk class I and consequent testing in a clinical trial.

It will be the aim of this retrospective analysis of the current observational study to obtain data so that a study protocol can be derived from this including a proof of mechanism for a then certified MD.

A large-scale prospective randomised controlled trial shall be planned to prove the main hypothesis and further to be identified secondary hypotheses to test the splints as medical device.

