## **6. Number of patients / volunteers**

Five volunteers (+ the inventor) have used the MD. Data from these volunteers shall be analysed.

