## **7. Statistics**

This is a retrospective analysis. Most likely, data of some variables will be missing. Data from weight courses/visceral fat from the last 10 years shall be analysed. Most likely only weight courses might be documented. This will only have been done according to clinical necessity. There will be no standardisation regarding time points.

All continuous variables shall be checked for normal distribution with the Kolmogorov-Smirnov test. Data shall be expressed as mean expressed as mean  $\pm$  standard deviation. Normally distributed variables shall be analysed with the two-sided t-test. Not normally distributed variables shall be analysed with the Mann-Whitney-U Test. Comparison of categorical variables shall be generated with the Pearson  $\chi^2$ -test and the Fishers exact test. The linear regression analysis shall be used to identify independent predictors for weight reduction in the follow-up period. Is not expected that these tests shall be used regarding the small number of volunteers. Statistical significance shall be assumed if a null hypothesis can be rejected at  $p \leq 0.05$ . All statistical analysis shall be performed with SPSS 20 ®.

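### Mean ± SD is prescribed for continuous data whatever the normality check shows; with five volunteers plus the inventor, one large responder can carry the primary weight result

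*Protocol*

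**What the plan says.** Section 3.2 of the Protocol defines the main outcome: "The primary endpoint is weight reduction after using the splints". Section 6 gives the sample: "Five volunteers (+ the inventor) have used the MD". The analysed number is therefore five or six, depending on whether the inventor is counted, and the eligibility criteria in Section 8 can only lower it.

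Section 7 makes these statements on analysis:
- Distribution check: "All continuous variables shall be checked for normal distribution with the Kolmogorov-Smirnov test".
- Presentation: "Data shall be expressed as mean expressed as mean", continuing with ± standard deviation. No condition is attached.
- Choice of test: "Normally distributed variables shall be analysed with the two-sided t-test", and "Not normally distributed variables shall be analysed with the Mann-Whitney-U Test".
- Use of the tests: "Is not expected that these tests shall be used regarding the small number of volunteers".

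Section 7 also says that weight and visceral-fat histories going back ten years will be examined, and that measurement times are not standardised. It does not say how those histories will be shown. The Protocol names no median, range, confidence interval, count of users who lost weight, or per-person display.

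**The concern.** The normality check affects only the test. A variable found to be non-normal is still reported as mean ± SD, so the check does not influence the one output that is likely to appear. Because the section then sets the tests aside, the descriptive summary largely carries the primary endpoint.

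For five or six people this summary fits poorly. Each person contributes one fifth or one sixth of the mean, so a single large loss can produce a mean change that reads as a group effect. Mean and SD together do not say whether most users lost weight or only one did, and the hypothesis of persistent weight reduction in users depends on that distinction.

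**Working it through.** The Protocol states no effect size or SD, so there is no figure of its own to reproduce. The weight changes below are assumptions chosen to show how the summary behaves. They are not trial data.

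**Inputs.** n = 5 or 6 (Section 6); summary = mean ± SD (Section 7); assumed pattern: one user loses d kg and the others change by 0.

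**Formulas.** Mean = -d/n. The sum of squares about the mean is d²(1 - 1/n), so SD = √[d²(1 - 1/n)/(n - 1)] = d/√n. The standard error is SD/√n = d/n, which equals the size of the mean. The t-based 95% CI is mean ± t(0.975, n - 1) × d/n.

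**Results for d = 20 kg.**
- n = 5: mean = -20/5 = -4.0; SD = 20/√5 = 8.94; CI = -4.0 ± 2.776 × 4.0 = -15.1 to +7.1. Median 0; one of five lost weight.
- n = 6: mean = -20/6 = -3.33; SD = 20/√6 = 8.16; CI = -3.33 ± 2.571 × 3.33 = -11.9 to +5.2. Median 0; one of six lost weight.

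**Range of d.** For d from 10 to 30 kg, the mean runs from -2.0 to -6.0 (n = 5) or from -1.67 to -5.0 (n = 6). The median stays at 0. Because mean and standard error are equal in size, t is always -1 (two-sided p = 0.374 or 0.363), and the CI always includes 0. The 20 kg means also fall within the 1.5 to 4.5 kg that Section 2 gives for an energy-deficit diet, so nothing in their size would alert a reader.

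**The summary does not identify the pattern.** At n = 6, three users at -10.8 kg and three at +4.1 kg give the same -3.3 ± 8.2 kg as one user at -20 and five at 0.

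**If absolute weights are summarised.** Section 4 lists weight after use, not change, as the target variable. Assume baselines of 82, 88, 94, 99, 105 and 118 kg with changes of -0.5, +0.5, 0, -1, 0 and -20 kg. Mean ± SD is 97.7 ± 12.8 before and 94.2 ± 8.2 after. The mean falls by 3.5 kg, the SD becomes smaller, and the median change is -0.25 kg. Here the SD gives no hint that one person accounts for nearly all of the fall.

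**The case against.** The strongest reply is that naming one summary does not exclude others, and that medians, listings and plots are commonly left to a statistical analysis plan, which is not shown here. That stands as far as silence goes. The point is narrower: the Protocol states a presentation rule, leaves it unchanged when normality fails, and applies it to five or six people.

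Several limits also stand:
- A reader might infer that the rule covers every variable. It directly follows the sentence on continuous variables and cannot sensibly apply to the yes/no items in Section 4.
- A reader might infer that mean ± SD is the entire result. The weight histories are also to be examined, so it is only the main stated summary.
- The SD is a partial warning. In the single-responder example SD/|mean| = √n, about 2.2 to 2.4. It is also wrong to say that precision is unavailable, because mean, SD and n determine the t-interval.
- The example is an extreme, and the t-intervals assume a normality that it violates by construction. They serve only as illustration.
- A reader might infer that the later randomised trial will be sized on this SD. Section 3.2 says only that the aim is "to obtain data so that a study protocol can be derived from this". It names no SD or mean change as a planning input, so the documents do not support that reading.

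**Conclusion.** The point holds in limited form. For continuous data, Section 7 fixes mean ± SD regardless of the distribution check and does not expect the tests to be used. With five volunteers plus the inventor, the primary weight result then rests largely on a summary that one large responder can drive and that hides how many users lost weight. Under the assumed pattern (one of five loses 20 kg, the rest 0), the report would be -4.0 ± 8.9 kg with a median of 0.

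The kilogram figures depend on that assumed pattern. The mechanism does not: one person's change always moves the mean by one fifth or one sixth of its size. This is a weakness of presentation, not an error that invalidates the analysis. It is best labelled a cheap improvement.

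**What to change.** Replace the mean ± SD sentence in Section 7 with a rule for weight change along these lines:

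1. List or plot each user's weight change from time point 0 against months since time point 0. Use pseudonymised codes and relative time rather than calendar dates, in keeping with the data-protection terms in Section 9.
2. Summarise change by the median (minimum-maximum) and by the number of users below baseline at the last documented visit, out of all users analysed. The last visit gives the count a defined assessment point although visits are not standardised; its date is already among the target variables in Section 4.
3. Give any mean change only alongside these, with its 95% CI and a note that the interval assumes normality.

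The individual display is the main item. A count alone treats a trivial fall as a loss: in the absolute-weight example above, three of six users are below baseline, two of them by 1 kg or less.

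The cost is a few lines of wording and one table or plot for five or six people. The headline figure may look less favourable. No new data are needed.

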#### Target variables

- **weight, BMI and waist circumference after using the MD**
- duration of follow-up (in month all years)
- number of follow-up visits
- date of last follow-up visit
  
- Concurrent medication
- change of medication during follow-up (y/n), which?
  
- Laboratory findings:
  - HLP, HBA1C, hs-CRP, BB,
- Sports or physical activity
- adherence of using the MD
- subjective details regarding the MD
- change of eating behaviour
- psychologic statement of the personnel of the medical practice of [name]
- change of quality of life and physical performance

Time point 0 is the visit at which the patient decided to use the MD.

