### **5. Study design**

This is a retrospective analysis to be carried out after obtaining written informed consent of the volunteers that their data shall be used for scientific research (see appendix).

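### Section 7 names no paired method for a within-person primary endpoint: Mann-Whitney U does not fit, the t-test is not stated to be paired, and the normality check is idle at n = 5 or 6

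*Protocol*

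**What the plan says.** Section 3.2 of the protocol sets the endpoint: "The primary endpoint is weight reduction after using the splints". Section 4 (Target variables) fixes the reference point: "Time point 0 is the visit at which the patient decided to use the MD". Section 6 gives the sample: "Five volunteers (+ the inventor) have used the MD. Data from these volunteers shall be analysed". Section 8 makes receipt of the device an inclusion criterion, and no comparison group is described anywhere.

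Section 7 then gives general rules without tying any of them to the primary endpoint:

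- Gate: "All continuous variables shall be checked for normal distribution with the Kolmogorov-Smirnov test".
- Normal variables go to a two-sided t-test; paired or unpaired is not stated.
- Otherwise: "Not normally distributed variables shall be analysed with the Mann-Whitney-U Test".
- Categorical variables are compared with Pearson chi-square and Fisher's exact test.
- Regression: "The linear regression analysis shall be used to identify independent predictors for weight reduction in the follow-up period".

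The section adds that, with so few volunteers, use of these tests is not expected. The next sentence sets significance at p ≤ 0.05.

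**The concern.** Each person supplies both the before and the after weight, so the relevant variation is that of the individual changes. Mann-Whitney U compares two unrelated groups. The only way to apply it to the primary endpoint here is to treat the before and after weights of the same people as if they came from different people. An unpaired t-test would do the same. Either puts the spread of body weight between people into the error term, and with five or six people that can hide a real loss.

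The rule that chooses between the tests does not help, because a normality test on five or six values hardly ever rejects. A regression meant to isolate independent predictors has almost no residual information. What remains is a 0.05 threshold, a list of tests of which none is stated in a form that suits the main question, and a forecast that they will probably not be run. The results are meant to inform a later protocol and a randomised trial (Section 3.2), so the reader of those results needs to know how the weight change was estimated.

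**Working it through.** The protocol gives no power, effect size, SD or before-after correlation, so there is no figure of its own to reproduce.

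**Inputs from the protocol.** n = 5, or 6 if the inventor is counted (Section 6); one group, change from time point 0 (Sections 3.2 and 4); threshold 0.05 (Section 7).

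**Assumptions, for illustration only.** SD of weight 15 kg at both times; true mean loss 10 kg; before-after correlation ρ of 0.80, 0.90 or 0.95; bivariate normal data.

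**1. Error term.** Unpaired SE = SD·√(2/n). Paired SE = SD·√(2(1−ρ)/n). The ratio is 1/√(1−ρ), which depends on neither SD nor n. At n = 5 the unpaired SE is 15·√(2/5) = 9.49 kg.

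| ρ | SD of change, 15·√(2(1−ρ)) | Paired SE, n = 5 | Ratio |
|---|---|---|---|
| 0.80 | 9.49 kg | 4.24 kg | 2.2 |
| 0.90 | 6.71 kg | 3.00 kg | 3.2 |
| 0.95 | 4.74 kg | 2.12 kg | 4.5 |

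**2. Power for a 10 kg loss** (40,000 simulated data sets per setting, two-sided 0.05; the three figures are for ρ = 0.80 / 0.90 / 0.95).

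| Test | n = 5 | n = 6 |
|---|---|---|
| Paired t | 44 / 71 / 93% | 55 / 83 / 98% |
| Unpaired t | 8 / 7 / 7% | 9 / 8 / 7% |
| Mann-Whitney U | 5 / 4 / 4% | 8 / 7 / 7% |

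With no true change, the unpaired t-test rejects in at most 0.3% of data sets and Mann-Whitney U in at most 0.15%, against the nominal 5%. The error therefore costs power and does not create false positives.

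**3. Normality gate** (100,000 samples per distribution; mean and SD estimated from the sample). The standard 5% critical values are 0.563 (n = 5) and 0.519 (n = 6). There were no rejections for normal, exponential, lognormal, t (3 df) or uniform data at either size.

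A hand check agrees. Take a sample in which all values but one are equal. The equal values standardise to −1/√n, and the statistic is (n−1)/n − Φ(−1/√n):

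- n = 5: 0.800 − 0.327 = 0.473, below 0.563.
- n = 6: 0.833 − 0.342 = 0.492, below 0.519.

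With Lilliefors critical values, which allow for the estimated mean and SD, detection was 14% (n = 5) and 17% (n = 6) for exponential data, and 20% and 27% for lognormal data.

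**4. Regression.** Residual degrees of freedom are n − 1 − k for k predictors. At n = 5, three predictors leave 1 and four leave 0.

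**5. What paired exact tests can reach.** For the signed-rank test the smallest two-sided p is 2/2ⁿ: 2/32 = 0.0625 at n = 5 and 2/64 = 0.031 at n = 6. Exact McNemar has the same floor when every pair changes in the same direction. At n = 5 neither can meet p ≤ 0.05, whatever the data show.

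**The case against.** The strongest defence is Section 7's own remark that the tests are not expected to be used. A reader might infer from the list of tests that the primary result will be analysed with the wrong error term. The documents do not support that: the tests may never be run, and no test is assigned to the primary endpoint. The t-test is unspecified, not unpaired. Since the gate almost never rejects, weight would normally go to that t-test and Mann-Whitney U would seldom be reached. A statistical analysis plan, not shown here, could specify the paired form.

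Three other strong readings also fail:

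- Chi-square and Fisher's test are confined to categorical variables, so they are not planned for weight.
- Section 7 plans mean and SD but no confidence intervals, so no planned interval is wrong. It also names no predictors, so it cannot be said to regress on the whole baseline list.
- The mismatch raises no risk of a false efficacy claim, because it is conservative.

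These points reduce the size of the problem without removing it. The remark about use is a forecast, not a rule. It offers nothing in place of the tests beyond mean and SD, and it stands next to a significance threshold. Section 3.1 says the hypothesis is to be tested, and Section 3.2 says efficacy is to be proven. The only nonparametric test named is still the wrong kind for the main question.

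**Conclusion.** The point holds as a should-fix. Section 7 states rules that do not fit a single-group, within-person endpoint, selects between them with a check that has almost no power at n = 5 or 6, and leaves open whether any test will be run. The primary endpoint therefore has no suitable stated analysis.

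The size is conditional. Only if before and after weights were compared as independent samples would the standard error be 2.2 to 4.5 times too large and power at n = 5 fall to about 4-8% from 44-93%. The SE ratio rests on the assumed correlations alone. The power figures also rest on the assumed 15 kg SD, 10 kg loss and normality. The gate result and the floors on exact p-values need no assumption about weight SD or effect.

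**What to change.** In Section 7:

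- Replace the Kolmogorov-Smirnov, t-test and Mann-Whitney sentences with a listing and plot of every participant's weight course, plus the mean paired change from time point 0 to a stated post-use visit (for example, the last documented follow-up) with a t-based 95% confidence interval. A stated visit is needed because the section says time points are not standardised.
- Treat any signed-rank or exact McNemar test as supportive only, and give its smallest two-sided p: 0.0625 at n = 5 and 0.031 at n = 6.
- Delete the regression for independent predictors, and keep chi-square and Fisher's test out of before-after comparisons.
- Replace the forecast about use of the tests and the p ≤ 0.05 threshold with one statement that the analysis is descriptive.

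In Section 6, state whether the inventor is analysed, so that n is 5 or 6.

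The cost is a few sentences and no new data. The interval will be wide: at n = 5 its half-width is 2.776 × the paired SE, about 5.9 to 11.8 kg under the assumptions above (2.776 × 2.12 and 2.776 × 4.24). The plan also gives up a formal significance claim, which it could hardly support at this size; the testing and proof wording in Sections 3.1 and 3.2 should be brought into line.

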## **8. Inclusion and exclusion criteria**

### **Inclusion criteria**

1. age: 18 to 95 years
2. gender male and female
3. ability to consent
4. written informed consent
5. exploit of the established evidenced-based options for weight reduction
6. receiving an MD
7. at least two documented visits after receiving the MD

### **Exclusion criteria for the analysis**

1. weight reduction of at least 5% during the last six weeks before receiving and using the MD
2. wasting disease
3. taking medication that affects weight (steroids, psychoactive medication, diuretics , etc.)
4. pregnancy or breastfeeding mothers
5. reduce compliance or psychological disorders
6. inability to consent
7. participating in another clinical study

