#### **3.1. What is expected?**

From this analysis of the first volunteers the hypothesis shall be tested that

- there was a continuous increase of weight and of the visceral fat over the last 10 years related to the baseline weight when they splints were first used

- there will be a weight reduction and reduction of the visceral fat and now weight regain, even after stopping using the splints.

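### Exclusion 1 drops users with a recent large weight loss from the whole analysis, which tilts the pre-device hypothesis in Section 3.1 in its own favour without guaranteeing it

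*Protocol*

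**What the plan says.** Protocol Section 3.1 introduces its two expectations with "From this analysis of the first volunteers the hypothesis shall be tested that". The first is that "there was a continuous increase of weight and of the visceral fat over the last 10 years related to the baseline weight", the baseline being the weight when the splints were first used. The second concerns loss after the device.

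Section 3.2 fixes the primary endpoint: "The primary endpoint is weight reduction after using the splints". Section 4 defines the start: "Time point 0 is the visit at which the patient decided to use the MD".

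Section 6 gives the series: "Five volunteers (+ the inventor) have used the MD. Data from these volunteers shall be analysed". Section 7 adds: "Data from weight courses/visceral fat from the last 10 years shall be analysed".

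The exclusion list in Section 8 is headed "Exclusion criteria for the analysis". Its first item is "weight reduction of at least 5% during the last six weeks before receiving and using the MD". Nothing in the protocol limits this item to the post-device analysis, and no item excludes recent weight gain.

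**The concern.** One eligibility list serves two hypotheses with different needs. For loss after the device, removing users who were already losing weight quickly is sensible, since otherwise an ongoing loss could be credited to the splints. For the pre-device hypothesis the outcome is the weight course up to first use, and the six-week window is the last part of it. A user with a large late fall is the kind of user who weakens a claim of continuous increase, and that user is removed before the course is described.

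There is no control group, so the pre-device course is the background against which any loss on the splints will be read. If part of the rise comes from the eligibility rule, the turn at device start looks sharper than it was among the actual users. Section 3.2 intends these data to shape a later trial protocol, so the description would be carried forward.

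**Working it through.** The protocol gives no effect size, variability or sample size calculation, so it has no figure to reproduce. The check has three parts.

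**1. Direction.** The threshold (a loss of at least 5%), the window (six weeks) and the scope (the whole analysis) come from Section 8. The outcome (the ten-year course to first use) comes from Section 3.1. Removing only low values of the final six-week change raises the mean of that change in those who remain. With no true trend, the shift in the ten-year change is therefore upward or nil.

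**2. Average size with no true trend.** Assume that weight, as a percentage of the user's mean, is a stationary Gaussian process with standard deviation SD and correlation exp(−t/τ) at a lag of t weeks. Both SD (4% to 8%) and τ (13 to 52 weeks) are assumptions.

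- Six-week correlation: r = exp(−6/τ)
- SD of the six-week change: s = SD × √(2(1 − r))
- Share removed: p = Φ(−5/s)
- Mean six-week change in those kept: m = s × φ(5/s)/(1 − p)
- The covariance of the weight at first use with the six-week change is half the variance of that change, and the weight ten years earlier is practically uncorrelated with it. The spurious ten-year rise is therefore m/2.

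Low end (SD 4%, τ 52): r = 0.891 and s = 1.867%. Then p = Φ(−2.68) = 0.0037, m = 1.867 × 0.0111/0.9963 = 0.021%, and the shift is 0.01%.

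High end (SD 8%, τ 13): r = 0.630 and s = 6.879%. Then p = Φ(−0.727) = 0.234, m = 6.879 × 0.3063/0.7663 = 2.75%, and the shift is 1.4%.

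| SD, τ | s | Share removed | Spurious mean rise | Chance that at least 1 of 5 / of 6 is removed |
|---|---|---|---|---|
| 4%, 52 wk | 1.87% | 0.4% | 0.01% | 2% / 2% |
| 4%, 13 wk | 3.44% | 7.3% | 0.26% | 32% / 37% |
| 8%, 52 wk | 3.73% | 9.0% | 0.33% | 38% / 43% |
| 8%, 13 wk | 6.88% | 23% | 1.4% | 74% / 80% |

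The last column is 1 − (1 − p)^n.

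A second model shows how many contrary users stay in. It takes the ten-year change as an independent long-term part (SD 4% or 8%) plus a six-week part with s from 2% to 5%. The rule then removes about 1% to 30% of users with a net decline, so most remain. The share of retained users with a net rise moves from 50% to between 50% and 59%.

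**3. A single removal.** Suppose four users each gain 5 kg over ten years. A fifth also gains 5 kg, to 90 kg, then loses 5% (0.05 × 90 = 4.5 kg) in the last six weeks and ends 0.5 kg up.

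- All five: (4 × 5 + 0.5)/5 = 4.1 kg, all five with a net rise, one course clearly not continuous.
- After exclusion 1: (4 × 5)/4 = 5.0 kg, four of four.

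The difference is 0.9 kg, and the one broken course is no longer described.

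**The case against.** The strongest reply is that the rule is narrow. It acts on the last six weeks of a window of about 520 weeks and only on falls of 5% or more. A flat course, a slow decline, an earlier large loss or a recent loss under 5% all stay in. A reader might infer that the group has been selected to confirm the rise. The documents do not support that: the hypothesis can still fail, and someone removed for a late fall may still have a net gain over the ten years. This stands, and it limits the point to a partial tilt.

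The size also rests on assumptions. At the top of the range, s is 6.9%, so about 47% of users would gain or lose at least 5% in any six weeks, which is extreme. At the bottom the average effect is negligible. This stands too.

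The primary endpoint is unaffected, and Section 7 does not expect the formal tests to be used with so few volunteers. That makes a false significance claim unlikely. It does not remove the tilt, since means and individual courses would still be described after the deletion.

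No user is shown to meet exclusion 1. Weights were recorded only when clinically needed, so the six-week window may not be assessable for everyone. Users also enter only after trying established weight-reduction options and are followed from the visit at which they chose the device. The pre-device course would therefore remain that of a selected group even without exclusion 1. All of this is fair. It lowers the severity but is no reason to leave in place a one-directional selection that is easily removed.

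**Conclusion.** The point holds in a limited form. As written, exclusion 1 makes the first Section 3.1 hypothesis depend on the end of its own outcome, in the direction that favours it. It does not make confirmation certain, and it does not distort the primary endpoint, for which the exclusion is reasonable.

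The average effect is small to moderate and cannot be pinned down from the protocol: about 0.01% to 1.4% of body weight under no true trend, given the assumed SD and correlation time. The practical weight of the point lies in the series of five or six, where one removal can change what is described. Whether any removal occurs is unknown. Severity is minor.

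**What to change.** Add a statement to Section 8 that exclusion 1 applies only to the analysis of weight change after the device. Describe the ten-year pre-device course in all consenting users regardless of exclusion 1. Report how many users the rule would have removed, mark them in the table of individual courses, and mark separately those whose records do not allow the six-week window to be assessed.

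The cost is one sentence in the protocol and a marker in a table. The weight records are already being extracted, no new data are needed, and the analysis of the primary endpoint does not change.

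### The two-visit rule, and possibly the undefined compliance exclusion, choose the analysis set on behaviour after the device was received, in conflict with Sections 3.1, 4 and 6

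*Protocol*

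**What the plan says.** Section 8 of the protocol sets the analysis set. Inclusion criterion 7 requires "at least two documented visits after receiving the MD". The second list is headed "Exclusion criteria for the analysis", and its item 5 reads "reduce compliance or psychological disorders". Reduced compliance is given no definition, threshold or period.

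Four other places bear on this:

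- Section 4, Target variables, fixes the time origin: "Time point 0 is the visit at which the patient decided to use the MD". The same list includes "adherence of using the MD" and the number of follow-up visits.
- Section 5 states the design: "This is a retrospective analysis to be carried out after obtaining written informed consent of the volunteers".
- Section 6 says: "Five volunteers (+ the inventor) have used the MD. Data from these volunteers shall be analysed".
- Section 3.1 expects weight loss without regain, including after the splints are no longer used (taking the printed wording there as a typing slip for no regain).

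Section 3.2 makes weight reduction the primary endpoint and proof of efficacy the primary aim. The results are also to inform the protocol of a later trial.

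**The concern.** There is no control group, so the evidence for efficacy is the weight change in the people who enter the analysis. Who enters therefore matters as much as how weight is measured. The visit rule acts after time point 0 by its own wording. The compliance rule is applied when each person's use of the device and weight course can already be known, and nothing confines it to the period before the device.

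If people who comply less or return less often also lose less weight, these filters remove the poorer results and raise the mean loss. They also shorten the range of two variables that the study sets out to describe, and they may remove people who stopped using the device, who are the ones needed for the hypothesis about weight after stopping. Section 2 itself calls quitting and regain major problems of weight programmes, and these filters could hide both. A selected estimate would then carry over into the design of the later trial.

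**Working it through.** The plan gives no effect size, standard deviation or power figure, so there is nothing to reproduce. The check has two parts: comparing the sections, and sizing the possible bias.

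**Comparing the sections**

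- *Section 8 against Section 6.* Section 6 takes the known users as the people to be analysed and makes no reservation. Section 8 can remove some of them for what they did after receiving the device.
- *Section 8 against Section 4.* Adherence and number of visits are variables to report, but low values of each can be grounds for removal.
- *Section 8 against Section 3.1.* A person who stops using the splints could be classed as poorly compliant, yet is needed to see whether weight is regained.
- *Section 8 against Section 5, Origin of data.* Volunteers who are not patients of the practice may supply data by telephone. Such a person can have a known outcome without two documented visits.

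**Sizing the bias**

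Inputs: n = 5 users (Section 6, without the inventor). Assumptions: the true mean change is zero, changes are normal, and the one or two users ranked lowest on compliance or return are dropped. That ranking has correlation ρ with weight loss. The documents give no value for ρ or for the number dropped, so both are varied.

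The expected normal order statistics for n = 5 are −1.163, −0.495, 0, 0.495 and 1.163. The expected mean among those kept, in SD units, is ρ times the average of the order statistics kept:

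- one dropped: ρ × (−0.495 + 0 + 0.495 + 1.163)/4 = ρ × 1.163/4 = ρ × 0.291
- two dropped: ρ × (0 + 0.495 + 1.163)/3 = ρ × 1.658/3 = ρ × 0.553

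| ρ | One of five dropped | Two of five dropped |
|---|---|---|
| 0 | 0 | 0 |
| 0.3 | 0.09 SD | 0.17 SD |
| 0.5 | 0.15 SD | 0.28 SD |
| 0.7 | 0.20 SD | 0.39 SD |
| 1.0 | 0.29 SD | 0.55 SD |

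A simulation of 500,000 sets gives the same values to two decimals. With six users (inventor included), over ρ = 0.3 to 1.0, it gives 0.08 to 0.25 SD for one dropped and 0.14 to 0.48 SD for two.

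*In kilograms.* The documents give no SD of weight change. If it were 5 kg (an assumption), one dropped gives 0.09 × 5 ≈ 0.4 kg up to 0.291 × 5 ≈ 1.45 kg. Two dropped gives 0.166 × 5 ≈ 0.8 kg up to 0.553 × 5 ≈ 2.8 kg. Half or double that SD halves or doubles each figure. Section 2 credits an ordinary energy deficit with about 1.5 to 4.5 kg. At 5 kg, one exclusion stays just below that range even at ρ = 1. Two exclusions reach it only when ρ is above about 1.5/2.76 = 0.54.

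*False positives.* For a one-sample t-test on change at two-sided 0.05, the chance of a significant result in the weight-loss direction under no effect is 2.5% with all five kept. With two dropped it is 5.4% at ρ = 0.5 and 13.9% at ρ = 1.0. With one dropped it is 4.3% and 8.3%.

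**The case against.** The strongest reply is that the compliance exclusion may describe a trait known before the device was given. It is paired with psychological disorders and stands among patient-state criteria such as pregnancy and inability to consent. That reading is plausible, so it cannot be said as fact that this exclusion acts after treatment starts. What remains is that the text does not confine it to that period. The visit rule allows no such reading.

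Second, the criteria may remove nobody, since Section 6 names the known users as those to be analysed. This stands as far as it goes: no passage shows that anyone would be excluded. Equally, Section 6 does not say outright that every user is analysed whatever Section 8 says. The two sections pull against each other and need to be reconciled.

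Third, the direction of bias is not documented. Section 7 says weights were recorded as clinical need arose, at no standard times, so few visits need not mean failure and many may reflect illness. At zero correlation there is no bias. The 45% of quitters in Section 2 concerns other programmes and cannot be taken as a rate for this device.

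Fourth, repeated follow-up serves the question of persistence, which a single later weight cannot answer. That is a good reason to show the subset with two or more visits, but not to let it define the main set.

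Finally, Section 7 does not expect significance tests to be used with so few people, and Section 3.2 leaves proof of the main hypothesis to a planned randomised trial. The false-positive figures are therefore illustrative, and the harm falls on the descriptive mean and on what is concluded from it. Section 3.2 nonetheless states proof of efficacy as the primary aim here, so the point keeps its weight.

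**Conclusion.** The point holds in this form. Inclusion 7 selects the analysis set on behaviour after the device was received, and exclusion 5 can do so because it is undefined, has no time limit and is applied in retrospect. Both conflict with Sections 3.1, 4 and 6.

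Under no true effect, with five users and a correlation of 0.3 to 1.0 between compliance or return and weight loss, the mean shifts in the device's favour by about 0.09 to 0.29 SD if one is dropped and about 0.17 to 0.55 SD if two are. The upper ends are ceilings that require compliance to rank users exactly by weight loss. The correlation and the number dropped are assumptions.

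A reader might infer that the analysis is built to keep only the successes, that an effect would be created from nothing, or that adherence could no longer be described at all. The document does not support these. The direction depends on an unstated correlation, it is not known whether anyone would be removed, and adherence can still vary among those kept, though over a shortened range.

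**What to change.** In Section 8, delete reduced compliance from exclusion 5 and delete inclusion 7. Then:

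- Define the main set as every consenting device recipient who meets the remaining criteria, and align Section 6 with this.
- Show each person's documented weights with dates, marked as taken during or after device use. Follow-up was not standardised and Section 3.1 separates the two periods.
- List anyone without a later weight by category of reason, without identifying the person, and state how many of all recipients contribute to the mean change.
- Report adherence and number of visits per person as descriptors.
- Show the subset with at least two later visits only as a sensitivity display.

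The cost is two deletions, a sentence defining the main set and a few lines on presentation. No new data source is needed. The reported result may be less favourable, and follow-up lengths will differ between persons. Restricting the set to those who consent is still a selection made after the fact, but Sections 5 and 9 require consent, and stating the number of all recipients makes that selection visible.
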